### Statistical analyses

#### Clinical effectiveness

The trial will be conducted in compliance with the study protocol, the Declaration of Helsinki and GCP. Aiming at an intention-to-treat design we will include all participants who will be randomly assigned to conditions. Additionally, per protocol analyses (PPA) will be conducted, including only participants’ satisfying protocol treatment. Analyses of variance will be conducted to explore the effects of the treatments on all primary and secondary outcomes. Missing data will be handled using multiple imputations (MI). MI is especially robust with respect to missing data
[69]. For all analyses, Cohen’s d
[70] will be calculated by standardising the differences between baseline and follow-up scores by the pooled standard deviation of the baseline scores. We will also calculate the number needed-to-be-treated (NNT) with GET.ON Stress minimal guided and unguided to achieve one response compared to the control group. For all statistical analyses, significance level will be set at p < .05, one-sided. The effectiveness evaluation will be conducted in accordance with the CONSORT statement
[71].

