**Methods:**

A three-armed randomised controlled trial (RCT) will be conducted to compare a minimal guided and unguided iSMI with a waiting list control condition (WLC). Both active conditions are based on the same iSMI, i.e. GET.ON Stress, and differ only with regard to the guidance format. Employees with heightened levels of perceived stress (PSS ≥ 22) will be randomised to one of three conditions. Primary outcome will be comparative changes in perceived stress (PSS). Secondary outcomes include changes in self-reported depression, work-engagement, presenteeism and absenteeism. Moreover, a cost-effectiveness analysis will be conducted from a societal perspective, including both direct medical costs and costs related to productivity losses. In addition, a cost-benefit analysis will be conducted from the employer’s perspective. Incremental net-benefit regression analyses will address the question if there are any baseline factors (i.e. subgroups of employees) associated with particularly favorable cost-effectiveness when the experimental intervention is offered. Assessments take place at baseline, 7 weeks post-treatment and 6 months after randomisation.

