## Methods

### Design

A three-armed randomised controlled trial (RCT) will be conducted to compare minimal guided and unguided iSMI (GET.ON Stress) with a waiting list control condition (WLC). All intervention arms will have full access to treatment as usual (TAU). To control for potential confounding effects, TAU will be monitored. Assessments will take place at baseline (T1), post-treatment (7 weeks, T2), and at 6-months follow-up (T3; see Figure 
1 for a detailed overview of assessments). All procedures involved in the study will be consistent with the generally accepted standards of ethical practice. The study was approved by the University of Marburg ethics committee (No. 2014-5K). The trial is registered in the German clinical trials register under DRKS00005687.

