### Primary and secondary outcomes

Primary outcome will be perceived stress at post-treatment. In secondary analyses, we will explore the effects of the intervention on depression, anxiety, emotional exhaustion, quality of life, absenteeism/presenteeism and numbers of participants displaying a reliable positive change. Economic analyses will be conducted assessing cost-effectiveness and cost-utility from a societal perspective including the costs of all types of health services and the costs that stem from productivity losses. Additionally, cost-benefit analyses from an employer’s perspective will be conducted. In explorative analyses we will also investigate whether there are any baseline factors (i.e. subgroups of employees) associated with particularly favorable cost-effectiveness when the experimental intervention is offered.

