### Sample size calculation

We aim to include 408 participants. The study was designed based on the expected superiority of the active groups (minimal guided and unguided internet-based self-help) compared to the waiting-list control group on the primary outcome variable (i.e. perceived stress) at post-test. Based on pilot-evaluation data we expect a mean effect for the minimal guided treatment arm compared to the waiting list control group of d = 0.70. However, unguided internet-based interventions consistently produce lower effect sizes as guided interventions
[15] and a meta-analysis on traditional face-to-face interventions for work-related stress
[6] yielded an overall combined effect size of only d = 0.34. As we also want to examine the difference in the effectiveness of minimal guided and the unguided iSMI we aim to be able to detect difference between groups with an effect size of d = 0.30. Thus we need to include 408 participants. This sample will allow us to detect a between-group effect size (ES) of d = 0.30 with a power (1-ß) of 80 % and an alpha of .05 (calculated using PASS 12) in a one-tailed test (for uni-directional hypotheses H1: WLC < unguided < minimal guided iSMI).

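### The primary outcome is given both as a post-treatment PSS level and as a change in PSS, and the only analysis named (analysis of variance, with no baseline covariate) does not settle which is tested

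*Protocol article*

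**What the plan says.** **Outcome as a level.** The section Primary and secondary outcomes states: "Primary outcome will be perceived stress at post-treatment". Sample size calculation likewise refers to perceived stress at post-test.

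**Outcome as a change.** The abstract's Methods paragraph states: "Primary outcome will be comparative changes in perceived stress (PSS"). The limitations paragraph of the Discussion says that the study is powered for between-group differences in how far perceived stress is reduced.

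**Analysis.** Statistical analyses, Clinical effectiveness, states: "Analyses of variance will be conducted to explore the effects of the treatments on all primary and secondary outcomes". It does not say one-way, repeated-measures or covariate-adjusted. The same section computes Cohen's d from baseline to follow-up differences, divided by the pooled baseline SD. It plans multiple imputation and a one-sided 5% level.

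**Sample size.** "We aim to include 408 participants", a number meant to "detect a between-group effect size (ES) of d = 0.30 with a power (1-ß) of 80 % and an alpha of .05", one-tailed. No correlation with baseline enters the calculation.

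**Baseline data.** Table 2 ticks the PSS at screening (T0), baseline (T1), 7 weeks (T2) and 6 months (T3). Entry requires a PSS-10 score of at least 22.

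**The concern.** With two time points, a group-by-time analysis of variance is the same test as an unadjusted comparison of change scores. A one-way analysis of variance on T2 scores is a different test. In a randomised trial both estimate the same expected difference between arms, but their error variances differ, and so will their p-values in any one data set. The article describes the primary outcome in words that fit each, and its analysis sentence fits both.

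Two things follow. First, a reader cannot tell from the article which test is primary, or which form of the outcome the 408 participants were sized for. Second, neither unadjusted form makes the best use of the T1 PSS, which is already collected. The comparison most exposed is minimal guided versus unguided, because Sample size calculation ties the d = 0.30 target to it and the sample has almost no margin above 80% power.

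**Working it through.** **Inputs from the article:** 408 participants, three arms, d = 0.30, one-sided alpha 0.05, 80% power.

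**Assumed, because not stated:** 1:1:1 allocation (408/3 = 136 per arm), complete data, equal PSS variance at T1 and T2, and r, the T1 to T2 correlation, between 0.3 and 0.7.

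**Step 1: reproduce the plan's figure.** The normal approximation gives n per arm = 2(1.645 + 0.842)²/0.30² = 137.4, so 138 per arm or 414 in total. The planned 408 is within 3% of this. At 136 per arm the noncentrality is 0.30 × √(136/2) = 2.47, and the noncentral t with 270 degrees of freedom gives 79.5% power. The stated 80% is therefore the power of a plain unadjusted two-group comparison.

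**Step 2: error variance of each analysis, relative to the variance of T2 scores.**
- T2 scores, unadjusted: 1
- Change scores, unadjusted: 2(1 − r)
- ANCOVA on T1: 1 − r²

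The effective standardised difference is 0.30 divided by the square root of each. For example, at r = 0.3 it is 0.30/√1.4 = 0.254 for change and 0.30/√0.91 = 0.314 for ANCOVA.

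**Step 3: power at 136 per arm (noncentral t, one-sided 5%).**

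| r (assumed) | T2 scores, unadjusted | Change, unadjusted | ANCOVA |
|---|---|---|---|
| 0.3 | 79.5% | 67.0% | 82.7% |
| 0.4 | 79.5% | 72.8% | 85.3% |
| 0.5 | 79.5% | 79.5% | 88.6% |
| 0.6 | 79.5% | 86.7% | 92.5% |
| 0.7 | 79.5% | 93.8% | 96.5% |

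**Step 4: why ANCOVA is never the worse choice here.** Since 1 − r² is at most 1, it is never less precise than the T2 comparison. The excess variance of change over ANCOVA is 2(1 − r) − (1 − r²) = (1 − r)², which cannot be negative.

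**Step 5: where change falls below plan.** 2(1 − r) exceeds 1 when r is under 0.5. If the T1 SD is k times the T2 SD, the relative variance of change is 1 + k² − 2rk, which exceeds 1 when r is under k/2. If selection at entry makes T1 less variable than T2 (k below 1), the break-even lies below 0.5.

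**Step 6: a missing-data illustration (assumed, not from the article).** The article gives no dropout figure. If 20% of T2 scores were missing and imputation recovered nothing, about 109 per arm would remain (136 × 0.8 = 108.8). Power would be 71.3% for unadjusted T2 scores and, at r = 0.5, 81.7% for ANCOVA.

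**The case against.** The strongest reply is that the article never says the analysis is unadjusted. Analyses of variance is a generic plural that can cover repeated-measures models and, used loosely, ANCOVA. Covariates and model form are the kind of detail a condensed article leaves to a fuller plan. This stands: silence on a covariate is not a decision against one.

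A reader might also infer that the planned analysis throws away power already built into the sample size. The documents do not support that. The calculation took no credit for baseline, so an unadjusted comparison of T2 scores keeps its planned power of about 80% with complete data, and what is forgone is an extra gain.

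Nor can it be said that the change version is underpowered. It is below plan only at low r and above plan at high r. Selection at PSS 22 or more makes a low r plausible but does not show it. The criterion is applied in the screening questionnaires, and Table 2 lists T0 and T1 separately, so if T1 is a separate measurement its range is restricted only indirectly.

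Finally, the section that defines the outcome does fix a post-treatment level, an unadjusted comparison in a randomised trial is unbiased, and a choice of test after seeing data is a possibility rather than something the text shows. All of that is fair. What remains is that the article describes its primary outcome in two ways. It also contradicts itself on what was powered: a post-test level in Sample size calculation, a reduction in the Discussion. An inconsistency in what is written is not a detail deferred to another document.

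**Conclusion.** The point holds as an inconsistency plus a free improvement. The primary outcome is a level in two places and a change or reduction in two others, and the single analysis sentence does not decide between them.

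Its size depends on r, which is unknown. Over r from 0.3 to 0.7, an unadjusted change analysis has between 67.0% and 93.8% power for d = 0.30, against a constant 79.5% for unadjusted T2 scores. ANCOVA adds about 3 points to the latter at r = 0.3 (82.7 − 79.5), 9 at r = 0.5 (88.6 − 79.5) and 17 at r = 0.7 (96.5 − 79.5). These figures assume equal allocation, equal variances at T1 and T2, and complete data. That the outcome is stated in two forms rests on none of these assumptions.

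**What to change.** State in Clinical effectiveness that the primary outcome is PSS-10 at T2 (7 weeks), analysed by ANCOVA with arm as factor and T1 PSS-10 as covariate, fitted within each imputed data set and then pooled. Analyse each secondary continuous outcome measured at baseline in the same way, with its own baseline value as covariate. Reword the abstract and the limitations paragraph of the Discussion to match the definition in Primary and secondary outcomes. If any power statement allows for missing data, label the rate as an assumption.

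The cost is wording only. T1 PSS is already collected, no further participants or assessments are needed, and the 408 need not change. If a fuller analysis plan already specifies this model, only the article's outcome wording has to be aligned with it.

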### Aims

Thus, this study aims at strengthening the evidence-base for internet- and mobile-based SMI (iSMI) by investigating the acceptability and (cost-) effectiveness of minimal guided and unguided iSMI in employees with heightened levels of perceived stress.

The study has the following specific aims: (1) To assess the effectiveness of minimal guided and unguided versions of iSMI for reducing perceived stress when compared to a waiting list control group (WLC). (2) To assess the comparative effectiveness of minimal guided and unguided iSMI. (3) To assess the cost-effectiveness of minimal guided and unguided iSMI compared to WLC. (4) To assess the comparative cost-effectiveness of minimal guided and unguided iSMI from a societal perspective. (5) To assess the cost to benefit ratio and return-on-investment of offering the interventions from an employer’s perspective. (6) To assess and compare acceptability of minimal guided and unguided iSMI. (7) To investigate in explorative analyses if there are any baseline factors (i.e. subgroups of employees) associated with particularly favourable cost-effectiveness when the experimental intervention is offered.

We hypothesise minimal guided and unguided iSMI both to be more effective and cost-effective than WLC; minimal guided iSMI to show higher effectiveness, cost-effectiveness and acceptability than unguided iSMI. Likewise, we expect guided iSMI to represent a better business case as seen from an employer’s perspective than unguided iSMI and WLC, respectively.

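### The blanket one-sided 5% rule does not fit an overall three-arm ANOVA, and the three directional claims behind the sample size have no named contrasts or gate

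*Protocol article*

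**What the plan says.** The Clinical effectiveness section names analyses of variance for all primary and secondary outcomes. It does not say whether these are overall three-arm tests or pairwise ones. It then sets one rule for everything: "For all statistical analyses, significance level will be set at" p < .05, one-sided.

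The Aims section gives three directional claims. Two are joint: "We hypothesise minimal guided and unguided iSMI both to be more effective and cost-effective than WLC". The third is that minimal guided beats unguided.

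The Sample size calculation section says "We aim to include 408 participants". The targeted difference is given as "we aim to be able to detect difference between groups with an effect size of d = 0.30", and the section ties this to the guided versus unguided question. The calculation is made "with a power (1-ß) of 80 % and an alpha of .05", "in a one-tailed test (for uni-directional hypotheses H1: WLC < unguided < minimal guided iSMI".

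The primary outcome is perceived stress at post-treatment, so there is one endpoint at one time point. No contrast, testing order, gate or alpha adjustment is stated.

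**The concern.** Three things do not fit together.

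- **Test and rule.** With three arms, the plain reading of an analysis of variance is an F-test with two numerator degrees of freedom. It has no direction, so a one-sided level has no meaning for it.
- **Powered test and named test.** The trial is sized on a one-sided comparison of two arms. An overall F-test can be significant because both active arms beat the waiting list, and it then says nothing about guidance. Yet guided versus unguided is Aim 2 and the reason given for d = 0.30.
- **Three claims, one level.** If each claim is tested by itself at one-sided 5%, the chance of some false claim on the primary outcome can exceed 5%.

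The rule also reaches every secondary outcome. The Background and Discussion treat the choice between guided and unguided as open, but under this rule a secondary result favouring unguided could not be declared significant. If the point is left open, the choice between an F-test and three separate tests could be made after the data are seen.

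**Working it through.** **Inputs.** From Sample size calculation: N = 408, d = 0.30, power 80%, one-sided alpha 0.05, expected d = 0.70 for guided versus waiting list, and d = 0.34 from the cited meta-analysis of face-to-face interventions. The allocation ratio is not stated; 1:1:1 is assumed, so 408/3 = 136 per arm. Effects are in SD units, with larger meaning less stress. W, U and G denote waiting list, unguided and minimal guided.

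**1. Reproduce 408.** n per arm = 2(z₀.₉₅ + z₀.₈₀)²/d² = 2(1.645 + 0.842)²/0.09 ≈ 137.4, so 138 per arm and 414 in all, within 3% of 408. Power at 136 per arm = Φ(0.30·√(136/2) − 1.645) = Φ(2.474 − 1.645) = 79.6% (79.5% with the t distribution). A two-sided 5% test needs 175 per arm, 525 in all, and does not reproduce. So 408 is a one-sided two-group calculation.

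**2. What an overall F-test would detect.** Noncentrality is λ = 136·Σ(μᵢ − μ̄)², with 2 and 405 degrees of freedom, at the 5% level.

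| True means (W, U, G) | λ | Power |
|---|---|---|
| 0, 0, 0.30 | 8.16 | 72.3% |
| 0, 0.40, 0.70 | 33.5 | above 99.9% |
| 0, 0.70, 0.70 | 44.4 | above 99.9% |

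The second row uses the planned effects (0.70 − 0.30 = 0.40 for unguided). In the third row guidance adds nothing, and the F-test is still almost certain to be significant. It therefore cannot carry the guided versus unguided claim.

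**3. Error rate of three ungated one-sided 5% tests.** With equal arms, U−W and G−U correlate at −0.5, and each correlates at 0.5 with G−W. The three statistics are projections of a two-dimensional standard normal on directions 60° apart. Hence P(any > 1.645) = (1/2π)∫exp(−1.645²/(2m(θ)²))dθ, where m(θ) is the largest of the three cosines and the integral runs where m > 0.

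- All three arms equal: 12.56% (12.5% in a simulation of 10 million draws).
- The two waiting-list comparisons alone: 8.8%.
- Guided truly better than waiting list (G > W): U ≤ W and G ≤ U cannot both hold, since together they give G ≤ W. At most one of the claims can then be false, so the rate is at most 5%.

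**4. Error rate with a gate on G versus W.** If G ≤ W, any rejection needs the gate to be passed wrongly, which has probability at most 5%. If G > W, at most one remaining null is true, again at most 5%. So familywise error is at most 5% with no order between the other two contrasts. Simulation under equal arms gives 5.0%.

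**5. Power for guided versus unguided (d = 0.30, 136 per arm).**

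| Rule | Power |
|---|---|
| Gate on G vs W only | 79.6% |
| Three-step order, unguided d = 0.40 (guided 0.70) | 74.8% |
| Three-step order, unguided d = 0.34 (guided 0.64) | 67.7% |
| Bonferroni, one-sided 0.05/3 | 63.5% (588 in all for 80%) |

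The gate itself has power above 99.9% at d = 0.70.

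**The case against.** The strongest reply is that the article never says overall F-test. A pairwise analysis of variance has one degree of freedom, F equals t², and it can be made directional. The sample size, which powers a pairwise difference, suits that reading. This stands as far as it goes: the mismatch depends on the overall reading. But no contrast is named, so the text does not settle the reading.

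Second, the two main charges pull apart. If a 5% overall F-test gated the pairwise tests, the false-claim rate would be 3.2% with equal arms and at most about 5% when only one pair is equal. A single trend contrast, or a rule that all comparisons must succeed, would also hold 5%. That is correct, but the article commits to none of these.

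Third, a reader might infer that the trial simply carries a false-claim rate of about 12.5%. The document does not support that. The figure is the maximum, reached only if all arms are equal and the three tests are ungated; it is not the error of an analysis of variance. Under the article's own expectation for guided versus waiting list, the rate is at most 5%.

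Fourth, a reader might infer that adverse results would go unseen. They would not. Reliable deterioration is counted, Cohen's d is reported for all analyses, and the cost-effectiveness section plans bootstrap intervals for costs and effects. What is missing is a significance test in that direction.

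Fifth, a separate analysis plan may supply a testing order. It could. It could not use two-sided tests for secondary outcomes without departing from the stated rule.

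**Conclusion.** The concern holds in limited form. The article fixes a one-sided 5% level for all analyses and names only analyses of variance, while the trial is sized on a one-sided pairwise test. On the overall reading, the level cannot be applied and the guided versus unguided question is not tested. On the pairwise reading, the level can be applied, but the contrasts are unnamed and ungated, with a false-claim rate of up to 12.56% if all arms are equal and at most 5% if guided truly beats the waiting list. These figures assume 1:1:1 allocation, normal statistics and no gate.

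On either reading, no secondary result against the expected direction can be declared significant. That follows from what the article states and does not depend on an unseen analysis plan.

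**What to change.** Name three one-degree-of-freedom contrasts on the PSS at T2 as the confirmatory analysis. Test minimal guided versus waiting list first, at one-sided 5%. Only if it is significant, test unguided versus waiting list and minimal guided versus unguided, each at one-sided 5%, with no order between them. Report two-sided 90% intervals, which match the one-sided 5% level, alongside 95% intervals. Use two-sided tests and intervals for secondary outcomes.

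The change is to wording only. N stays at 408, familywise error is 5%, and guided versus unguided keeps about 79.6% power under the planned effects, which a full three-step order would not.

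There are costs. If guided versus waiting list fails, the other two contrasts become descriptive, which is unlikely at d = 0.70. Two-sided testing makes secondary results slightly less favourable. On the primary outcome, a result favouring unguided over guided would still show only through its interval, because that contrast stays one-sided. Moving it to two-sided 5% would leave 69.6% power at 136 per arm.

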#### Cost-effectiveness and cost-utility analyses

In the cost-effectiveness analyses, treatment response (reliable positive change) will be the primary outcome, whereas quality adjusted life years (QALYs) will be the outcome in the cost-utility analyses. A cost-effectiveness acceptability curve
[72] will be calculated, when better outcomes are associated with higher costs. Such an acceptability curve represents the probability that the intervention is cost-effective relative to the control group, given varying thresholds for the willingness to pay (WTP) for gaining one additional treatment responder or gaining one additional QALY. Nonparametric bootstrapping will be applied to estimate confidence intervals for mean differences in costs and effects between groups.

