[76]. Second, we only include participants experiencing heightened levels of perceived stress, as indicated by a cutoff score of ≥ 22 on the Perceived Stress Scale. Thus, our results will only be generalisable to employees fulfilling this criterion. In occupational health routine practice SMI are often offered to the whole working population (i.e. universal prevention approach) instead of selecting participants based on baseline stress level. Therefore, future studies should evaluate this iSMI using a universal prevention approach to allow for a reliable estimation of efficacy and cost-effectiveness of the intervention for this target group. Finally, the study is powered to detect differences between groups in the reduction of perceived stress. Hence, the sample size will be too small to draw reliable conclusion for potential moderating effects between guided and unguided groups with regard to the clinical effectiveness of the intervention. Which participants are thus likely not to profit from unguided but from minimal guided iSMI will remain unclear. However, health-economic evaluations do not test hypotheses. Instead, a probabilistic decision-making approach is undertaken. Thus, this study will address the question “who benefits most?” in explorative analyses by relying on an incremental net-benefit regression analysis.

There will also be several strengths of this study, including the randomised controlled design with the direct comparison of two active conditions, an appropriate statistical analysis plan and handling of missing data with state of the art methods. Moreover, to the best of our knowledge, direct comparisons of the costs and benefits of different levels of support in internet-based occupational health management interventions have not been published so far.

Overall, to overcome the gap between the need for effective strategies for managing negative consequences of occupational stress and evidence-based treatment availability/utilisation, (cost-) effective low-threshold interventions are needed that are accessible for as many people as possible. Internet-based occupational health interventions might be a promising strategy to overcome some of the limitations of face-to-face occupational health interventions. This study will enhance the evidence-base for iSMI and provide information about the differential acceptability, efficacy and cost-effectiveness of two economic support forms in iSMI.

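### The acceptability curve is tied to a better-and-dearer point estimate, so elsewhere, notably if the intervention looks cheaper and better, no joint probability of cost-effectiveness across willingness-to-pay values is promised

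*Protocol article*

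**What the plan says.** The section on cost-effectiveness and cost-utility analyses names two effect measures: "treatment response (reliable positive change) will be the primary outcome, whereas quality adjusted life years (QALYs) will be the outcome" of the cost-utility analysis. It then says that an acceptability curve "will be calculated, when better outcomes are associated with higher costs", and explains that the curve "represents the probability that the intervention is cost-effective relative to the control group" at varying WTP for a responder or a QALY. The section closes with a commitment that carries no such condition: "Nonparametric bootstrapping will be applied to estimate confidence intervals for mean differences in costs and effects between groups".

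Other parts of the article bear on this:

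- Under primary and secondary outcomes, the societal perspective is described as "including the costs of all types of health services and the costs that stem from productivity losses".
- The section on the employer's cost-benefit analysis plans sensitivity analyses on the main cost-drivers.
- The section on incremental net-benefit regression builds net benefit from QALYs and calls the intervention cost-effective when the incremental net benefit is above €0.
- Aim 4 is "To assess the comparative cost-effectiveness of minimal guided and unguided iSMI from a societal perspective".
- The Discussion says that health-economic evaluation does not test hypotheses and that "a probabilistic decision-making approach is undertaken".

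**The concern.** The curve summarises the joint sampling distribution of the cost and effect differences. That distribution exists whichever quadrant of the cost-effectiveness plane the point estimate falls in, and so does the probability read from it. At a WTP of €0 the curve equals the probability that the intervention saves money, which is the figure needed to judge an apparent saving. The stated condition makes this display depend on the signs of two noisy estimates.

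The cost difference is shared by the responder and QALY analyses. A negative cost estimate therefore removes the commitment to both curves at once. Read literally, the condition also leaves out the cheaper-but-worse quadrant, where cost and effect again have to be traded off.

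At stake is the conclusion on value for money. The article says this rests on probabilities rather than tests, yet the curve is the only output that it defines as a probability.

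**Working it through.** **Step 1. What each planned output delivers if the estimate is cheaper and better.**

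- Acceptability curve: not promised, because the condition is not met.
- Bootstrap intervals: one for the cost difference and one for the effect difference. They are marginal and give no joint probability at any WTP.
- Sensitivity analyses: these vary the cost-drivers and do not describe sampling uncertainty.
- Net-benefit regression: joint in cost and QALY at a chosen WTP, and its coefficient would have a standard error. It does not cover treatment response, is introduced to study effect modification, and its stated criterion is only the sign of the net benefit.

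**Step 2. Arm size.** The article contests no number here; its total of 408 only sets the scale. With d = 0.30, one-sided alpha 0.05 and 80% power, n per arm = 2 × (1.645 + 0.842)² / 0.30² = 137.4, so 138, and 3 × 138 = 414. This is within 1.5% of 408. The allocation ratio is not stated, so equal arms are assumed: 408 / 3 = 136.

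**Step 3. Illustration.** Every cost and response figure below is an assumption: control response 25%, response gain 2 to 20 points, cost SD €2,000 to €10,000, saving €100 to €1,000. The cost and effect differences are taken as normal and independent.

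- SE of cost difference = SD × √(2/136) = 0.1213 × SD
- SE of response difference = √[(p0(1−p0) + p1(1−p1)) / 136]
- P(cost-effective) = Φ[(WTP × gain + saving) / √(WTP² × SE_E² + SE_C²)]

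The least certain case has SD €10,000, saving €100 and gain 2 points:

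- SE_C = 1,213 and SE_E = 0.0532.
- At WTP €0: Φ(100/1,213) = Φ(0.082) = 53%.
- At WTP €10,000 per responder: Φ(300 / √(532² + 1,213²)) = Φ(300/1,324) = 59%.
- P(true result cheaper and better) = Φ(0.082) × Φ(0.02/0.0532) = 0.533 × 0.647 = 34%.

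| Cost SD (€) | Saving (€) | Gain (points) | P(cheaper and better) | P(cost-effective), WTP €0 | P(cost-effective), WTP €10,000 |
|---|---|---|---|---|---|
| 10,000 | 100 | 2 | 34% | 53% | 59% |
| 10,000 | 100 | 20 | 53% | 53% | 94% |
| 5,000 | 500 | 10 | 77% | 80% | 97% |
| 2,000 | 1,000 | 20 | 100% | 100% | 100% |

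The point estimate is cheaper and better in all four rows. A simulation of 200,000 draws over the whole grid gave the same extremes: about 53% to 100% at €0 and about 59% to 100% at €10,000.

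**Step 4. Do the marginal intervals fill the gap?** Take the third row:

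- SE_C = 606, so the 95% interval for cost is −500 ± 1.96 × 606, from a saving of €1,688 to an extra €688.
- SE_E = 0.0552, so the interval for response is 10 ± 10.8 points, from −0.8 to 20.8.

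Both intervals include zero, yet at €10,000 per responder P(cost-effective) = Φ(1,500 / √(552² + 606²)) = Φ(1.83) = 97%. The two intervals alone do not tell the reader this.

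**The case against.** The strongest reply is that this is loose wording in a condensed article. The sentence does not say that a curve is ruled out elsewhere, and the Discussion's probabilistic approach is not limited to one quadrant. That is a fair reason for modest weight, but the condition is written down rather than merely left out, and no other sentence promises a curve or a probability of cost-effectiveness outside that quadrant.

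Three stronger readings are tempting, and the article does not support them.

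- *A cheaper-and-better result would be reported with no uncertainty.* It would not. The bootstrap intervals do not depend on the quadrant, and the regression can inform the QALY outcome. With an assumed saving of €100 and SE of €400, the planned cost interval would run from a saving of €884 to an extra €684 (−100 ± 1.96 × 400), so readers would see that the saving is not established.
- *Cheaper and better is the likely result.* Counting productivity losses makes it possible. The hypotheses predict better cost-effectiveness than waiting list, not lower societal cost. For guided versus unguided, the Background and Discussion stress the cost of coaching, which points towards the quadrant where the curve is promised.
- *Guided versus unguided is left out because the curve is described relative to control.* Those words explain what a curve is. Aim 4 already commits to that comparison, and the bootstrap is planned between groups generally.

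**Conclusion.** The point holds as a defect in one stated rule. Outside the better-and-dearer quadrant, the article promises no joint probability of cost-effectiveness across WTP values, and none at all for treatment response. This sits badly with its own description of the economic evaluation as probabilistic.

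The range in the working shows that a cheaper-and-better estimate can carry anything from near coin-flip to near-certain support. It rests on assumed costs and response rates, equal arms, normality and independence of the cost and effect differences. Reading it as a probability about the true difference also implies a flat prior, or equivalently treating bootstrap proportions as probabilities. It shows what could go unreported and does not forecast this trial's result.

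The weight is minor to moderate. This is a reporting rule for a secondary economic output; the primary analysis, sample size and data collection are untouched, and the curves could be drawn later from the same data.

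**What to change.** Delete the conditional clause and state, for example: *Acceptability curves will be calculated from the bootstrap replicates whatever the quadrant of the point estimate, for both treatment response and QALYs, and for each planned comparison: guided versus waiting list, unguided versus waiting list, and guided versus unguided.*

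Naming the third comparison ties the curve explicitly to Aim 4. A joint curve giving the probability that each of the three options has the highest net benefit would be a useful extra, but it is optional because Aims 3 and 4 are pairwise.

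The cost is about one sentence and a few more figures. The bootstrap is already planned, so no new data are needed, provided that cost and effect are resampled together within participants.
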